### Methods in analysis to handle protocol non-adherence and missing data {20c}

All analyses and data summaries will be conducted on the intention-to-treat (ITT) population which is defined as all participants randomised regardless of non-compliance with the protocol or withdrawal from the study.

If appropriate, a CACE analysis using the instrumental variable approach will be conducted to estimate the treatment effect for the primary outcome when accounting for non-compliance with the intervention.

Missing data is expected; the reasons (e.g. due to loss to follow-up, illness or at random) and mechanisms for missing data will be explored, and the proportion of missing data will be compared between the intervention and control groups and by participant baseline characteristics. The sample size calculation allowed for 25% loss to follow-up for the primary outcome.

For primary and secondary outcomes, a multiple imputation model will be built under the missing at random assumption with imputation at the individual participant level. Sensitivity analyses of the primary endpoint will be conducted to assess the impact of missing data, the choice of imputation model and the missing at random assumption, as appropriate.

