### Sample size {14}

The recruitment target is 565 participants equally distributed across standard care and intervention plus standard care. This will provide 90% power at 5% significance to detect a between-group difference of three points on CORE-OM (standardised effect size of 0.375) allowing for 25% loss to follow-up and design effect of 1.56. The design effect appropriately inflates the required sample size for an individually randomised controlled trial to account for clustering resulting from therapist-delivered intervention. The design effect assumes (i) cluster size of 11—on average each of 21 intervention therapists treat 15 patients, 11 provide follow-up data; (ii) coefficient of variation of 1.34 to account for variable numbers of patients per therapist (range 3–23) and (iii) intervention intra-cluster correlation coefficient (ICC) of 0.05 [35].

A similar design effect is assumed within the control arm: a wider range of therapists provide treatment as usual, resulting in fewer trial patients per standard care therapist (smaller cluster size) but potentially a higher ICC.

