## Statistical methods

### Statistical methods for primary and secondary outcomes {20a}

A detailed statistical analysis plan will be finalised and agreed by the research team prior to analysis.

A single final analysis is planned after the trial is closed to recruitment and follow-up and when the full database has been cleaned and locked. Analyses will be completed by the CTRU statisticians using SAS version 9.4.

The primary analysis of CORE-OM will use mixed multilevel linear regression with repeated measures (6- and 12-month outcome) adjusted for randomisation stratification factors and baseline value, with therapist treated as a random intercept. Estimated mean treatment differences at each time point will be reported with 95% confidence interval, *p*-values and ICCs. A two-sided 5% significance level will be used for statistical endpoint comparisons, unless otherwise specified.

Secondary outcomes, reliable and clinically significant improvement on the CORE-OM, hopelessness, depression and social connectedness will be analysed using the same approach, i.e. mixed multilevel linear or logistic regression, depending on the type of outcome variable.

Secondary outcomes repetition of self-harm leading to hospital and self-reported repetition of self-harm will be analysed separately.

Cox proportional hazards, accounting for randomisation stratification factors and random therapist effect (multilevel survival frailty model) [40], will be used to test for differences in the time to first repetition and the proportion of participants attending hospital for self-harm at 6 and 12 months. Hazard ratios and corresponding 95% CIs will be presented. If a participant is lost to follow-up, they will be treated as censored. Kaplan–Meier curves will be constructed for each group.

Recurrent event analysis incorporating the timing and cumulative number of hospital attendances for self-harm will be used to test for differences in the rate of recurrent events. Estimated treatment differences will be reported as the hazard ratio with 95% confidence interval and *p*-values.

Self-reported self-harm will be summarised at each follow-up time point (monthly to 12 months).

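### Read as single-level, the participant-level imputation conflicts with the therapist random intercept in the primary model: it attenuates the reported ICC and slightly understates the standard error

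*Protocol article*

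**What the plan says.** Three sections of the protocol article bear on this.

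- **Statistical methods {20a}.** CORE-OM is analysed by a multilevel linear model with 6- and 12-month scores as repeated measures, "adjusted for randomisation stratification factors and baseline value, with therapist treated as a random intercept". On reporting: "Estimated mean treatment differences at each time point will be reported with 95% confidence interval", together with p-values and ICCs. Most secondary outcomes follow the same approach.
- **Protocol non-adherence and missing data {20c}.** For primary and secondary outcomes, "a multiple imputation model will be built under the missing at random assumption with imputation at the individual participant level". The section then adds: "Sensitivity analyses of the primary endpoint will be conducted to assess the impact of missing data, the choice of imputation model" and the missing-at-random assumption, as appropriate. It does not list the variables in the imputation model, and it does not say whether imputed data feed the primary model or only supplement it.
- **Sample size {14}.** Therapist clustering is built into the design through an "intervention intra-cluster correlation coefficient (ICC) of 0.05" and a design effect of 1.56, with 25% loss to follow-up. A similar design effect is assumed in the control arm.

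**The concern.** An imputation model should contain at least the structure of the model fitted afterwards. Here the analysis model says that patients of one therapist resemble each other. A single-level imputation model draws missing scores as if they did not. About a quarter of outcomes would then enter the analysis with no therapist effect of their own, and this dilutes the between-therapist variance in the completed data.

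Two results are exposed. The first is the therapist ICC, which the plan promises to report and which later trials may use for their own sample sizes. Clustering assumptions also drove this trial's own sample-size re-estimation (Trial status). The second is the standard error of the treatment difference, which partly loses the allowance for clustering that the sample size paid for.

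The mixed model on the available 6- and 12-month scores is already valid under missing at random. Single-level imputation in front of it would therefore add a fault without adding a safeguard.

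**Working it through.** **1. The plan's own figures.** "This will provide 90% power at 5% significance to detect a between-group difference of three points on CORE-OM" and a "standardised effect size of 0.375" imply SD = 3 / 0.375 = 8.

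- Per arm, unclustered: 2 × (1.960 + 1.282)² × (8/3)² = 149.4, so 150.
- Total: 2 × 150 × 1.56 / 0.75 = 624. This is close to the abstract's 630 (and 21 × 15 = 315 per arm), not to the 565 in Sample size {14}.
- Design effect = 1 + ((CV² + 1)m − 1) × ICC with m = 11 and ICC = 0.05. The printed CV of 1.34 gives 2.49; a CV of 0.34 gives 1.56.

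These mismatches need reconciling, but they do not decide this point. I use 630, 21 therapists and CV 0.34 for the planned design.

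**2. Effect on the ICC.** With a fraction f missing at random and therapist left out of the imputation, a pair of patients of the same therapist keeps its covariance only if both were observed:

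ICC after imputation = ICC × (1 − f)² = 0.05 × 0.75² = 0.028, a cut of 44%. Cluster size does not enter.

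**3. Effect on the standard error** (closed form, outcome variance 1, no covariates, n per arm, m patients per therapist):

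- True variance of a clustered arm mean: V = [1 + ((CV² + 1)m(1 − f) − 1) × ICC] / [n(1 − f)]
- Rubin's variance: T = [1 + ((CV² + 1)m − 1) × ICC(1 − f)²] / n + [1/(n(1 − f)) − 1/n]
- Unclustered arm: V₀ = 1/[n(1 − f)]
- SE ratio = √[(T + V₀)/(V + V₀)] with clustering in the intervention arm only, or √(T/V) with equal clustering in both arms
- Type I error = 2 × [1 − Φ(1.96 × ratio)]

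For 630 participants and 21 therapists, n = 315, m = 15 and f = 0.25:

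- V = 1.5775 / 236.25 = 0.00668
- T = 1.4425 / 315 + 0.00106 = 0.00564
- V₀ = 1 / 236.25 = 0.00423
- Intervention arm only: √(0.00987 / 0.01091) = 0.951
- Both arms: √(0.00564 / 0.00668) = 0.919

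| Design (ICC 0.05, 25% missing) | Clustering | SE ratio | Type I error |
|---|---|---|---|
| 630, 21 therapists | intervention arm | 0.951 | 6.2% |
| 630, 21 therapists | both arms | 0.919 | 7.2% |
| 348, 32 therapists (assumed) | intervention arm | 0.984 | 5.4% |
| 348, 32 therapists (assumed) | both arms | 0.970 | 5.7% |
| 348, 50 therapists (assumed) | intervention arm | 0.992 | 5.2% |
| 348, 50 therapists (assumed) | both arms | 0.984 | 5.4% |

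**4. Simulations** (ICC 0.05, 25% missing):

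- 21 therapists × 15, imputing from baseline only (r = 0.5), 4,000 trials: mean SE 0.941 of the empirical SE; type I error 6.8%, against 5.4% for available cases; ICC 0.067 to 0.038 (−43%).
- 630 participants, 21 therapists, imputing from arm, baseline and 6-month score, 1,200 trials: model SE 0.0927 against 0.0975 for the observed-data mixed model (ratio 0.95); type I error 6.1% against 4.9%; ICC 0.059 to 0.039 (−34%). Therapist fixed effects in the imputation overcorrect: ICC 0.097, SE 0.107, type I error 2.2%.
- A third run (baseline r = 0.4, intervention-arm clustering): at 630 with 21 therapists, SE about 4% too small, type I error 6.1% against 5.1%, ICC 0.059 to 0.033 (−44%). At 348 with an assumed 32-48 therapists, SE about 1% too small, type I error 5.4-5.6%, ICC cut by over 40%.
- One small-cluster case, with about 48 therapists seeing 4 patients each, showed a smaller ICC loss, 0.063 to 0.047 (−25%), and no visible type I effect.

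**The case against.** The strongest reply is that the premise is not in the text. Imputing at participant level can simply name the unit imputed, a participant's score rather than a therapist-level value, and a model with a therapist random effect also does that. A reader might infer that the plan definitely ignores clustering. The article never says so, and it defers detail to an analysis plan that is not shown. This stands, and it is why the point is conditional. It does not remove the point: {20c} makes a positive statement about the level of imputation, and in a plan whose analysis is explicitly multilevel, single-level is a natural reading of it. The sensitivity analyses on the imputation model cover the primary endpoint only.

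A reader might also infer that the primary interval will be materially too narrow. The documents do not support that for the trial as it now stands. Trial status reports more therapists than assumed and a target of at least 348, and smaller clusters shrink the effect on the standard error to about 1-3%. Even at 21 therapists the evidence is modest. In the 1,200-trial run, 6.1% has a Monte Carlo standard error of about 0.7 points (√(0.061 × 0.939 / 1200)), and the imputed-data SE was 0.978 of its own empirical SD.

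Finally, {20a} already names the repeated-measures mixed model as the primary analysis. That is so, but {20c} leaves open whether imputed data enter it.

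**Conclusion.** The point holds conditionally. If the imputation is single-level, it is uncongenial with the therapist random-intercept model.

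- **ICC:** the firmer consequence. The reported value falls by roughly a third to 45%; one small-cluster run gave a quarter. The loss persists with more therapists.
- **Standard error:** about 4-6% too small under the planned 21-therapist design (type I error about 6-7%), reaching 8% (7.2%) in the closed form if the control arm is equally clustered. At 348 with 32-50 therapists it is about 1-3% too small (type I error about 5.2-5.7%).

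These sizes rest on assumptions the article does not supply: the correlations between baseline, 6- and 12-month scores (0.4 to 0.6), missingness unrelated to therapist, a CV of 0.34, equal residual variances, and the number of therapists at 348. The 32 is borrowed from the fidelity section {11c}; Trial status gives no count. This is a cheap improvement, chiefly to a promised result, and not a threat to the main conclusion.

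**What to change.** State two things in the protocol and the analysis plan:

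1. The likelihood-based repeated-measures mixed model, fitted to the available 6- and 12-month data, gives the primary result and the reported ICC.
2. Any multiple imputation, whether as a sensitivity analysis or for secondary outcomes, uses an imputation model whose clustering matches the analysis model, with a therapist random effect. Therapist fixed effects should not be used instead, because they overcorrected in the check above.

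If two-level imputation is already intended, one clarifying sentence is enough. The cost is the wording, modest extra programming, and possible convergence work where therapists have few patients.

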### Plans to give access to the full protocol, participant-level data and statistical code {31c}

Data will be available upon request and subject to approval by the Leeds CTRU and FRESHSTART CI. A legally binding data sharing agreement will be required prior to access/sharing of any study data.

## Oversight and monitoring

### Composition of the coordinating centre and trial steering committee {5d}

The *Programme Steering Committee (PSC)* will co-provide overall supervision of the programme grant and trial, in particular, study progress, adherence to protocol, participant safety and consideration of new information. It will include an independent chair, no fewer than two other independent members with appropriate clinical and statistical expertise, and a patient representative. The CI and other members of the Programme Management Group may attend the PSC meetings and present and report progress. The committee will meet once during the set-up period and at least annually thereafter for the duration of the study.

The* Programme Management Group* (PMG) will oversee the whole FReSH START Programme Grant, comprising the chief investigator, programme manager, co-applicants, co-investigators, and NHS host.

The* Trial Management Group* (TMG) comprises the chief investigator, the programme manager, key co-applicants, research fellows and CTRU staff. The TMG will meet at key points during the study to oversee the study including the set-up, on-going management, promotion of the study and the results.

A trial monitoring plan will be developed and agreed by the TMG and PSC based on the trial risk assessment which will consider the safety or physical or mental integrity of the trial participants and the scientific value of the research.

The* Lived Experience Group* (LEG) provides advice and accountability from people with lived experience of self-harm. The group will meet at regular intervals over the trial period based on group preferences and whenever research activity necessitates their input. Members will advise on study processes and materials, guide our communication with stakeholders and wider audiences and contribute to process evaluation data analysis and the development of dissemination plans and materials.

The trial is managed on a day-to-day basis by the CIs, the research fellows and core team at the Leeds CTRU who will regularly meet to discuss the study. They will be responsible for the set-up of the study, including gaining ethical and R&D approval, appointment of additional researchers if required, management and overall supervision of the study team, collection and analysis of data and drafting publications. The chief investigator will be responsible for the day-to-day running of study.

The CTRU will be responsible for the following: registration, randomisation system, database development and provision, CRF design, data management and quantitative design, analysis and reporting.

### Composition of the data monitoring committee, its role and reporting structure {21a}

A Data Monitoring and Ethics Committee (DMEC) will be convened to monitor data collected during the study and make recommendations to the PSC on whether there are any ethical or safety reasons as to why the trial should not continue. It will consist of an independent chair, an independent statistician and an independent clinician. The DMEC will meet annually as a minimum.

### Adverse event reporting and harms {22}

A serious adverse event (SAE) is any untoward medical occurrence that results in death, is life-threatening, requires inpatient hospitalisation or prolongation of existing hospitalisation, results in persistent or significant disability/incapacity, consists of a congenital anomaly or birth defect.

The National Research Ethics Service (NRES) defines related and unexpected SAEs (RUSAEs) as follows:‘Related’—that is, it resulted from administration of any research procedures; and‘Unexpected’—that is, the type of event is not listed in the protocol as an expected occurrence.

All related/unexpected SAEs occurring from the date of consent up to 12 months post-randomisation will be recorded on the related/unexpected serious adverse event (RUSAE) form and faxed to the CI within 24 h of the clinical research staff becoming aware of the event. All related/unexpected SAEs will be reviewed by the chief investigator, notified to the sponsor within one working day, and are subject to expedited reporting to the main REC by the CTRU on behalf of the chief investigator within 15 days. Events will be followed up until the event has resolved or a final outcome has been reached.

The following events are expected within the study population and will be collected from date of consent until 12 months post-randomisation: hospital admissions and re-admissions, life-threatening repeated self-harm not leading to hospital admission, death (including suicide).

In this population, the expected rate of deaths for those who self-harm is approximately 60–100 times that of the population as a whole; thus, it is possible that some people may die as a consequence of self-harm during the course of the study. As deaths are more likely within this population, they will not be subject to expedited reporting to the main REC, unless the PSC and DMEC advises that the frequency of self-harm related and/or all deaths observed within the trial population is significantly higher than that expected in the general self-harm population. All deaths occurring from the date of consent up to 12 months post-randomisation will be recorded on the death form and reported. The Data Monitoring and Ethics Committee (DMEC), funder, and sponsor will be informed of deaths (with the data available at the time) within 1 month of reporting by site.

Hospital admission details will be obtained by regular extracts from centralised hospital records via Hospital Episode Statistics from NHS digital (supplemented by researcher review of local hospital records).

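### Because expectedness depends only on a cause-free list, a death, admission or life-threatening self-harm episode judged to be caused by the therapy has no expedited reporting route

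*Protocol article*

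**What the plan says.** All of the relevant text is in the Protocol article, section Adverse event reporting and harms {22}.

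- **Serious** covers an event that "results in death, is life-threatening, requires inpatient hospitalisation or prolongation of existing hospitalisation", and also persistent or significant disability and congenital anomaly.
- **Related** means that "it resulted from administration of any research procedures".
- **Unexpected** means that "the type of event is not listed in the protocol as an expected occurrence".
- **The list of expected events** is "hospital admissions and re-admissions, life-threatening repeated self-harm not leading to hospital admission, death (including suicide". These are collected from consent to 12 months after randomisation.
- **Expedited route.** For related and unexpected events, the chief investigator must hear within 24 hours and the sponsor within one working day. On the ethics committee, the text says that such events "are subject to expedited reporting to the main REC by the CTRU on behalf of the chief investigator within 15 days".
- **Deaths.** Given the higher death rate among people who self-harm, the text says of deaths that "they will not be subject to expedited reporting to the main REC, unless the PSC and DMEC advises that the frequency" is too high. The comparison is of all deaths in the trial, or those linked to self-harm, with the general self-harm population, and the excess must be significant. Deaths go on a death form, and the DMEC, funder and sponsor are told within one month of the site's report.
- **Admissions.** "Hospital admission details will be obtained by regular extracts from centralised hospital records via Hospital Episode Statistics from NHS digital", with researcher review of local hospital records as a supplement.

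**The concern.** A list of expected events normally keeps background events out of the expedited stream. In a population that self-harms repeatedly, that is sensible. Here, however, the list is written largely as seriousness outcomes and not as event types with a cause. An admission is expected whatever led to it, and so is a death. Since the list alone decides expectedness, a site's judgement that the therapy caused the event makes no difference to the result.

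The protocol itself accepts that therapy may harm some participants. Section {11b} lets the therapist and clinical team stop therapy where continuing would raise the risk of harm. Section {10} excludes people whose mental state deteriorated severely after earlier talking treatments. If such harm occurred, it would most likely appear as a psychiatric admission, serious self-harm or suicide, and all three are on the list.

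Two things are at stake. One is prompt review by the chief investigator, sponsor and ethics committee of an individual case judged to be therapy-related. The other is the meaning of the RUSAE count when the trial reports harms.

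**Working it through.** The plan states no figure to reproduce, so the main check is a mapping. Each seriousness criterion in section {22} is set against the list of expected events, under the section's own definition of unexpected.

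| Seriousness criterion | On the expected list? | Can it be a RUSAE if judged related? |
|---|---|---|
| Death | Yes, any cause | No |
| Inpatient hospitalisation | Yes, any cause | No |
| Life-threatening | Yes if admitted, or if repeated self-harm without admission | Only if not self-harm and not admitted |
| Prolongation of an existing stay | Not named | Yes, on a plain reading |
| Persistent disability or incapacity | Not named | Yes, unless it also leads to admission |
| Congenital anomaly | Not named | Yes |

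Death and hospitalisation are closed completely, and the life-threatening criterion is closed for self-harm. What stays open is not the form that serious harm from a talking therapy would usually take.

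**Could the slash in the article's term related/unexpected be read as *or*?** The section introduces the category as related *and* unexpected and gives the two conditions joined by *and*. Even under the other reading, deaths would remain outside expedited ethics committee reporting because of their separate exemption.

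**Does the frequency trigger for deaths close the gap?** It acts on the number of deaths in the trial population, so it cannot bring forward a single death judged related. Its sensitivity can be illustrated, but only with assumptions. The article gives a multiple of 60–100 times the general population and no base rate, so I assume a 12-month death risk p of 0.5%, 1% or 2%. I also assume that significantly higher means a one-sided binomial test at 0.025.

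- Deaths X ~ Binomial(N, p), with N = 348, the revised minimum target in Trial status.
- Threshold r is the smallest r with P(X ≥ r | p) ≤ 0.025.
- The chance of reaching it if the risk is doubled across the whole trial is P(X ≥ r | 2p).

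| Assumed p | Expected deaths (348 × p) | r | P(X ≥ r given p) | P(X ≥ r given 2p) |
|---|---|---|---|---|
| 0.5% | 1.74 | 6 | 0.0087 | 0.139 |
| 1% | 3.48 | 9 | 0.0092 | 0.264 |
| 2% | 6.96 | 13 | 0.0247 | 0.638 |

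At N = 565, the target in section {14}, the thresholds are 8, 12 and 19 deaths and the chances are 0.209, 0.457 and 0.809. A doubling confined to the therapy arm would raise the pooled risk only to (p + 2p)/2 = 1.5p under 1:1 allocation, so these chances would be lower still. The committees are not bound to such a test. The table shows only that a pooled count is a blunt instrument across a plausible range.

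**The case against.** The strongest case on the other side is that this is a reasoned policy and not a slip. The article uses the related-and-unexpected category of the research ethics service, explains why deaths are common in this population, and adds a committee trigger. Listed events do not disappear:

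- They are collected to 12 months in both arms of a 1:1 randomised trial, so admissions and deaths can be compared by arm. With frequent background events, that comparison may be more informative than case-by-case causality.
- Hospital attendance for self-harm is analysed between arms as a secondary outcome (sections {12} and {20a}).
- Deaths reach the DMEC, funder and sponsor within a month. The DMEC receives safety summaries and can recommend stopping for safety (sections {21a} and {21b}).
- Therapists and clinical teams can end therapy for risk, and reasons for ending are recorded (sections {11b} and {11c}).

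All of this stands, and it rules out several stronger readings that a reader might infer:

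- *Such events escape all oversight.* They do not, as the points above show.
- *A therapy-related admission reaches the trial only through a routine-data extract.* The same sentence adds researcher review of local records.
- *Nobody records relatedness for listed events.* The article does not say so. The death form and the full protocol (version 6.0) are not shown, and form content is commonly left to them.
- *A nil RUSAE count would say nothing about safety.* Some event types can still qualify, and other safety evidence exists.

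These points do not supply the missing route. The DMEC is required to meet only once a year, and its summaries exclude primary and secondary outcome data (section {21b}). As self-harm attendance is a secondary outcome, the article leaves unclear how much of it the DMEC sees. Nor is this an effect of condensing the protocol: the definition, list, death exemption and timelines are all stated, and the difficulty lies in how they combine.

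**Conclusion.** The point holds for the expedited route. As published, a death, a hospital admission or a life-threatening self-harm episode without admission cannot be a RUSAE even when judged to result from the therapy. For deaths, the only alternative route to expedited ethics committee reporting is a pooled-frequency trigger. A low RUSAE count would therefore largely reflect the definition and should not by itself be offered as evidence of safety.

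It would go too far to say that no serious event can be unexpected, or that the count must be close to zero whatever the risk. The open criteria in the mapping remain, and the documents give no basis for predicting a count.

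The conclusion rests on the text of section {22} alone. The death-trigger figures are illustrative and depend on assumed risks; the conclusion does not need them. If version 6.0 already provides for related listed events, the remaining task is to reconcile the two texts. This is a recommended correction to safety reporting. It does not touch the primary estimate, its analysis or the randomised comparison of harms.

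**What to change.** In section {22}:

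1. State that the expected-event list and the death exemption apply only to events not judged related to trial therapy or procedures.
2. State that any serious event judged related, including a listed event or a death, goes on the RUSAE form and follows the existing timelines: 24 hours to the chief investigator, one working day to the sponsor, 15 days to the ethics committee.
3. Confirm that relatedness is recorded for deaths and for locally known admissions, and add it if the full protocol and forms do not already provide for it.

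Unrelated listed events stay non-expedited, so the purpose of the exemption is kept. The cost is a wording amendment, possibly one added form field, and a small number of extra expedited reports, limited to events judged related. If recruitment has closed by the time this is acted on, relatedness can still be assessed for deaths and known admissions before harms are reported, and the report can explain how the RUSAE definition limits that count.
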